## Section 9 – Statistics/Statistical Analysis Plan

### 9.1a *A description of the statistical methods to be employed, including timing of any planned interim analysis(es).*

Baseline characteristics will be expressed as numbers and percentages for categorical variables and median and interquartile range (IQR) for continuous variables. Differences between control and intervention baseline characteristics will be compared by chi-square or rank-sum as appropriate (for descriptive purposes since this is a cluster randomized trial and there may be chance imbalances due to case-mix during the intervention and control periods).

All analysis will be by intention to treat except where otherwise noted.

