#### Primary Outcome - Adverse Drug Events

A mixed-effects logistic regression model will be used for the outcome of adverse drug events ( $\geq 5$  on Leape-Bates scale) which controls for intervention, time period, and number of baseline potentially inappropriate medications as fixed effects and cluster as a random effect. This model will be used to estimate adjusted risk differences.

A sensitivity analysis will be conducted (supplemental) using a Leape-Bates Scale of  $\geq 4$  for the definition of adverse drug events.

This analysis will be conducted on patients who have consented to, and participated in, the post-discharge follow-up.

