##### - Proportion of patients with one or more PIMs stopped at discharge

A mixed-effects logistic regression model will be used for the outcome of stopping 1 or more PIM which controls for intervention, time period, and number of baseline potentially inappropriate medications as fixed effects and cluster as a random effect. This model will be

used to estimate adjusted risk differences. This analysis will be conducted on patients who are taking 1 or more PIM at admission and who are discharged alive from a study unit.

- ER Visit/Readmission within 30-days of hospital discharge

A mixed-effects logistic regression model will be used for the outcome of ER visit or readmission post discharge which controls for intervention, time period, frailty status, long-term care residence, age, gender and number of baseline potentially inappropriate medications as fixed effects and cluster as a random effect. This analysis will be conducted on patients who have consented to, and participated in, the post-discharge follow-up.

- Deaths within 30-days of hospital discharge

A mixed-effects logistic regression model will be used for the outcome of death post discharge which controls for intervention, time period, frailty status, HOMR score and number of baseline potentially inappropriate medications as fixed effects and cluster as a random effect. This analysis will be conducted on patients who have consented to, and participated in, the post-discharge follow-up.

- Falls within 30-days of hospital discharge

A mixed-effects logistic regression model will be used for the outcome of fall post discharge which controls for intervention, time period, frailty status, long-term care residence, age, gender and number of baseline potentially inappropriate medications as fixed effects and cluster as a random effect. This analysis will be conducted on patients who have consented to, and participated in, the post-discharge follow-up.

- Absolute number of medications at discharge

A generalized linear regression model will compare the number of medications at discharge controlling for intervention, time period, and the number of baseline medications as fixed effects and cluster as a random effect. This analysis will be conducted on all patients who are discharged alive on a study unit (see above re transitions of care).

- Absolute number of medications at 30 days post-discharge

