*Sensitivity analyses as indicated above.*

*9.1b A description of the post-hoc statistical methods to address imbalances between the cluster and the intervention groups*

We performed 5 post-hoc sensitivity analyses to address the low number of clusters in the study: 1) an analysis adjusting for patient factors that differed between groups by  $P < 0.01$ ; 2) treating clusters as a fixed-effect; an analysis with 3) a random and 4) fixed effect for hospital ( $n=11$ , in lieu of cluster) and 5) using permutation, a non-parametric method of evaluating for the weighted within period effect size.

*9.2 The number of subjects planned to be enrolled (sample size calculation)*

The expected proportion of medical patients who will experience an ADE after discharge is between 10 and 19%. For our power calculation we have used the midpoint, 15%. Type

1 error will be 5% and type 2 will be 20%. The cluster correlation expected is no more than 0.03. We wish to show an absolute decrease of four percent. An 8400-patient trial comprising 6 clusters who each recruit 200 patients per cluster-period will have 80% power to detect a change in ADE of from 15% to 11.2% or lower (an absolute risk reduction of 3.8%, number needed to treat 27). Implementation of this power calculation used the Stata function “steppedwedge” and followed the Hussey and Hughes approach.

*Revised prior to the recruitment of the first 200 patients to any cluster to:*

Three clusters will be created based on geographical location in Canada (Quebec, Ontario, Western Canada). These clusters are expected to enroll 500 subjects per time period for a total of 1 baseline and 3 randomized time-periods. The total number of patients will be 6000. With an estimated 15% adverse drug event rate, this will yield at least 80% power to detect an absolute difference of 4.8% (NNT 21) with an alpha of 0.05 and varying intra-cluster correlation ranging from 0.01 to 0.05.

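### The only listed analysis that adjusts the primary outcome for patient case-mix beyond PIM count picks its covariates by a between-group P<0.01, not by prognosis

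*Protocol*

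**What the plan says.** Protocol section 9.1a, Primary Outcome, gives a mixed-effects logistic model for ADEs "which controls for intervention, time period, and number of baseline potentially inappropriate medications as fixed effects and cluster as a random effect". The all-adverse-event model has the same terms. PIM count is the only patient-level covariate in either.

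The models for ER visit/readmission and for falls, also in section 9.1a, go further: "which controls for intervention, time period, frailty status, long-term care residence, age, gender and number of baseline potentially inappropriate medications as fixed effects". The death model adds frailty and the HOMR score.

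On baseline balance, section 9.1a says: "Differences between control and intervention baseline characteristics will be compared by chi-square or rank-sum as appropriate". It gives the purpose as "for descriptive purposes since this is a cluster randomized trial and there may be chance imbalances due to case-mix".

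Section 9.1b then states: "We performed 5 post-hoc sensitivity analyses to address the low number of clusters in the study". Item 1 is "an analysis adjusting for patient factors that differed between groups by" P<0.01. Items 2 to 5 treat cluster as fixed, use hospital as a random or a fixed effect, or use a permutation method. None of these four names a patient factor.

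**The concern.** Only the order in which three regions cross over is randomised, so randomisation cannot be relied on to balance patients between control and intervention periods, and section 9.1a itself expects case-mix imbalance. Two features add to the risk. Patients and staff are blinded to the objectives in the control phase only (section 4.3). The primary analysis is limited to patients who consented to and took part in follow-up. Participation could therefore differ by phase.

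A case-mix check on the ADE result is worth having, and item 1 of section 9.1b is the only one listed. Its criterion is a P value for baseline difference. That says nothing about whether a factor predicts ADEs, it tightens or loosens with sample size, and it leaves the covariate set to the data. A better list was at hand in the readmission and falls models. Sections 4.1 and 7.1 place readmission, death and falls under adverse events. A fall is thus adjusted for frailty when analysed alone but not when it counts as an adverse event or an ADE, and no reason is given.

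What is at stake is how much reassurance this sensitivity analysis can give. The primary estimate does not depend on it.

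**Working it through.** **Inputs from section 9.2.** 3 regions, 4 periods, 500 patients per region-period, 6000 in all; ADE rate 15%; detectable difference 4.8 points; ICC 0.01 to 0.05. With one region crossing per step, 6 region-periods are control and 6 intervention, so 3000 patients each.

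**The plan's own figure.** The Hussey and Hughes variance (two-sided alpha 0.05, variance at 15%, ICC as a share of total variance) gives power for 15% against 10.2% of 79.9%, 79.9% and 80.6% at ICC 0.01, 0.03 and 0.05. The detectable difference is 4.76 to 4.81 points. The stated 80% and 4.8 points reproduce to rounding, so 4.8 points is a fair yardstick.

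**What P<0.01 means at this size** (3000 per arm, patients treated as independent):
- 50% characteristic: 2.576 × √(0.25 × 2/3000) = 3.3 points.
- 30% characteristic: 2.576 × √(0.21 × 2/3000) = 3.0 points.
- Continuous variable: 2.576 × √(2/3000) = 0.067 SD.

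**How often a region-only factor is flagged.** Let m1, m2, m3 be the factor's mean in the first, second and third region to cross over. The intervention arm weights them 3:2:1 and the control arm 1:2:3, so the pooled contrast is

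(3m1 + 2m2 + m3)/6 − (m1 + 2m2 + 3m3)/6 = (m1 − m3)/3.

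Its variance relative to that assumed by an unclustered test is (1 − ICC) + (2·ICC/9)/(2/3000) = (1 − ICC) + 333·ICC.

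| ICC of the factor (assumed) | Variance ratio | SE ratio | P(abs. z > 2.576) |
|---|---|---|---|
| 0.01 | 4.32 | 2.08 | 22% |
| 0.03 | 10.97 | 3.31 | 44% |
| 0.05 | 17.62 | 4.20 | 54% |

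A simulation with a 30% factor and 20,000 replicates per setting gives 22%, 44% and 54%, and 1% at ICC 0. With a cluster autocorrelation of 0.8 the three become 23%, 46% and 56%. The protocol gives no ICC for baseline factors; the outcome's range is borrowed.

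**What the screen does not isolate.** The model holds cluster and period, so the remaining threat is a shift within region that tracks the intervention. If that shift is d in every intervention cell, the pooled contrast is d + (m1 − m3)/3, which mixes it with regional make-up.

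**Size of the effect (risks assumed).** Take ADE risk 20% in frail and 12% in other patients. An overall 15% then implies (15 − 12)/8 = 37.5% frail. The standard error of the arm difference is √(0.375 × 0.625 × 2/3000) = 1.25 points, and the P<0.01 cut is 2.576 × 1.25 = 3.2 points.
- A pooled 5-point imbalance gives z = 5/1.25 = 4.0 and would be selected. Its crude effect is 0.05 × 0.08 = 0.4 points.
- A pooled imbalance just under the cut shifts the crude risk difference by 0.032 × 0.08 = 0.26 points.
- For a 30% factor with an odds ratio of 2 for ADE, an imbalance at the cut shifts it by about 0.3 points.

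Against 4.8 points these are about 5% to 8%.

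**The case against.** The case against is substantial, and most of it stands.

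- The rule sits in one of five analyses labelled post hoc, and the primary estimate does not rest on it. This stands.
- Section 9.1b names no test. That the P values ignore clustering is inferred from section 9.1a, where the tests are called descriptive. This stands, so the flag rates are conditional.
- Flagging a region-only factor is redundant rather than harmful, because the model already carries a cluster term. This stands: 22% to 54% is not a rate of biased results.
- A large pooled imbalance in a strong predictor would be caught. This stands for the pooled contrast. It does not settle the within-region question, since regional differences can offset a real shift: in d + (m1 − m3)/3 the two terms may have opposite signs.
- The 0.26- to 0.4-point figures are shifts in a crude difference. Drift common to all regions is removed by the period term. This stands; the figures carry over to the planned estimate only if the imbalance tracks the intervention within region and period.
- Different outcomes may properly have different covariates, and leaving prognostic factors out of the primary model is not an error in itself. This stands. The subgroup factors in section 4.1 (sex, long-term care, frailty) do not fill the gap, since effect by subgroup is not adjustment.

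None of this defends choosing covariates by a baseline P value when a prognostic list already exists in the same document.

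**Conclusion.** The point holds as a weakness in one post-hoc robustness check. Item 1 of section 9.1b is the only listed analysis that adjusts ADEs for patient factors beyond PIM count, and it selects them by the wrong criterion. If the test is unclustered, much of what it flags is regional difference that the model already handles.

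The likely numerical effect is a few tenths of a percentage point. That rests on assumed risks, an assumed ICC for the factor and the planned 3000 per arm; several correlated imbalances could add up to more.

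A reader might infer two stronger things. One is that the primary ADE estimate is biased because frailty, age, sex and long-term-care residence are missing from its model. The protocol gives no imbalance conditional on region and period, so this is not shown. The other is that the primary model should be replaced. Section 9.1b reports its analyses in the past tense, so a switch now could be driven by results, which would be worse than the weakness criticised.

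**What to change.** In item 1 of section 9.1b, replace the P<0.01 selection with a fixed list chosen without regard to baseline P values and matching the readmission and falls models: age, sex, frailty status, long-term-care residence and number of baseline PIMs, optionally with number of baseline medications. Fit it for ADEs and for all adverse events, keep the period and cluster terms, report a risk difference standardised over the sample, and label it post hoc.

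Keep the section 9.1a model as primary. Make the fixed-list model primary only if outcomes by arm have not been seen, and say so in the text.

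The cost is a little extra analysis and the loss of any patients with missing covariates. The covariates already appear in other section 9.1a models, so no new data collection is needed.

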### *9.3 The level of significance to be used.*

An alpha of 0.05 will be used. There will be no adjustment for multiple comparisons.

### *9.4 Criteria for the termination of the trial.*

There are no stopping criteria for this trial as the timing of ADE adjudication and the order of randomization of the cluster trial design does not permit an implementable interim analysis.

### *9.5 Procedure for accounting for missing, unused, and spurious data.*

Significant attempts will be made to have complete data. In the event of missing data, complete case analysis or multiple imputation will be performed as are appropriate to the situation.

### *9.6 Procedures for reporting any deviation(s) from the original statistical plan (any deviation(s) from the original statistical plan should be described and justified in protocol and/or in the final report, as appropriate).*

Deviations will be clearly highlighted and the final clinicaltrials.gov submission will be updated accordingly.

### *9.7 The selection of subjects to be included in the analyses (e.g., all randomized subjects, all dosed subjects, all eligible subjects, evaluable subjects).*

All subjects who consent and receive a deprescribing report while in hospital and who survive to hospital discharge will be analyzed for the primary outcome (which occurs within 30-days of hospital discharge). Subjects who die in hospital will not be analyzed for the primary outcome as they cannot experience the primary outcome.

For measures of efficacy on deprescribing at discharge, the population of interest will be all subjects who have 1 or more potentially inappropriate medication identified at baseline and who

1073 are discharged alive from a study unit regardless of whether or not they complete the post-  
1074 discharge interview.  
1075  
1076

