In the control arm, all eligible participants will receive medication reconciliation at admission and discharge (current standard of care), and a structured follow-up phone interview to determine if they had an adverse event and adverse drug event within 30-days of hospital discharge. A prioritized deprescribing list will NOT be generated for patients during the control period of the study although the potentially inappropriate medications and any standard of care deprescribing decisions will be recorded.

During the intervention period, the medical teams will receive a printout with individualized and prioritized deprescribing opportunities: a) identifying the medication, b) explaining (with references and rationale) why that medication is potentially inappropriate and c) instructions on how to safely stop/taper the medication and what to look out for post discontinuation. The treating medical team will review these opportunities with the unit pharmacist and patient and subsequently appropriate candidate medications for deprescribing could be tapered or stopped by the most responsible physician on the CTU.

During the intervention period, for all patients who give consent for follow-up, the research assistants will provide a generic deprescribing brochure to inform them of the relevance of the study and the importance of medication review. Additionally, for those patients who are taking a proton pump inhibitor or a sedative hypnotic, they will receive corresponding patient-oriented educational material. The purpose of these brochures is to educate patients about the harmful effects of PPIs and sedative hypnotics. The patient brochures have been independently designed by the Canadian Deprescribing Network with input from patient stakeholders and the information is presented in lay terms in both French and English. Copies of each of the brochures are available online.

Proton pump inhibitors: <http://www.criugm.qc.ca/fichier/pdf/PPI-EN-Men.pdf>

Sedative hypnotics/sleeping pills: <http://www.criugm.qc.ca/fichier/pdf/BENZOeng.pdf>

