## Section 6 – Treatment of Subjects

### *6.1 The intervention to be administered, including a description of the intervention, the timing, the method of administration, the follow-up period in the intervention and control arms*

The intervention consists of an electronically generated deprescribing report. A trained research assistant will collect the past medical history and certain lab values from the electronic chart and the medical admission note. They will enter this information along with the best possible medication history. The medication history will be elicited by a pharmacist or pharmacy technician. The information will be entered into the software MedSafer and a report will be generated based on cross-referencing with rules based on the existing evidence-based guidelines for deprescribing.

The report will only be generated after the medication reconciliation is performed by the pharmacist. In general, the report will be provided as soon as possible to the treating team and could be on day 0 or admission and up to day 3 of admission depending on resources on the unit and weekday or weekend admission status.

The team is free to act on the reports as per their local practice. At their own discretion, teams may choose to review reports at sign out, during rounds with pharmacists or prior to discharge.

Reports could be acted upon (or not) prior to hospital discharge. The discharge prescription is used as the final determination of whether deprescribing reports are acted on.

Participants who are taking sleeping pills or PPIs will also receive a brochure from the Canadian Deprescribing Network detailing the rationale for deprescribing this medication. All participants will receive a one-page study brochure that explains the rationale behind deprescribing which is available at <https://pamphlet.medsafer.org>

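### Section 9.7 makes receipt of a deprescribing report a condition of the primary analysis, which contradicts Sections 2.2 and 9.1a

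*Protocol*

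**What the plan says.** The protocol describes who enters the primary analysis in two places, and the descriptions differ.

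- Section 9.7, the section on selecting subjects for analysis, says of the primary outcome: "All subjects who consent and receive a deprescribing report while in hospital and who survive to hospital discharge will be analyzed". It adds that patients who die in hospital are left out.
- Section 9.1a, under the primary outcome: "This analysis will be conducted on patients who have consented to, and participated in, the post-discharge follow-up". There is no report condition here. The model is a mixed-effects logistic regression "which controls for intervention, time period, and number of baseline potentially inappropriate medications as fixed effects and cluster as a random effect".

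Three other statements bear on the point.

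- Section 2.2, on the control arm: "A prioritized deprescribing list will NOT be generated for patients during the control period of the study". Control patients do get the 30-day interview, and their potentially inappropriate medications are recorded.
- Section 9.1a, general rule: "All analysis will be by intention to treat except where otherwise noted".
- Section 6.1, on delivery of the report in the intervention phase: it may come on the day of admission or "up to day 3 of admission depending on resources on the unit and weekday or weekend admission status". Teams are free to act on it or not.

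**The concern.** A report can be received only after a patient's cluster has crossed to the intervention, and only after enrolment. It therefore cannot define a set that has to contain both phases. Read word for word, Section 9.7 admits no control patient.

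That will not be carried out, so what matters is how the sentence gets repaired in practice. The easy repair is to apply the condition where it can be met, in intervention periods, and waive it in control periods. Patients who consented but got no report would then leave the intervention side, while patients of the same kind remain on the control side. Whether a report is delivered may depend on length of stay, staffing and day of admission, and these may relate to the risk of an ADE. The comparison would become one of recipients against all controls. It would no longer be the effect of the cluster crossing over, which is what a stepped design with an intention-to-treat rule is built to estimate.

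**Working it through.** **1. The design as planned (Section 9.2, revised).** There are three clusters ("Three clusters will be created based on geographical location in Canada (Quebec, Ontario, Western Canada"), four periods (one baseline and three randomised) and 500 patients per cluster-period. The total is 3 × 4 × 500 = 6000, as stated.

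Power was checked with the Hussey and Hughes variance. One cluster is assumed to cross per period (the diagram is not shown) and alpha is assumed two-sided:

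Var = I·s·(s + T·t) / [(I·U − W)·s + (U² + I·T·U − T·W − I·V)·t]

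- Here I = 3, T = 4, U = 6 and W = V = 14, so I·U − W = 4 and the second bracket is 36 + 72 − 56 − 42 = 10.
- At an intra-cluster correlation of 0.03 and control-rate variance 0.15 × 0.85 = 0.1275: s = 0.1275 × 0.97/500 = 0.000247 and t = 0.03 × 0.1275 = 0.003825.
- Var = 0.000294, SE = 0.01715, and 0.048/0.01715 − 1.96 = 0.84, so power is 0.799.
- At correlations of 0.01 and 0.05, power is 0.799 and 0.806.

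The stated 80% for 4.8 points is reproduced. The sample-size figures are not at fault.

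**2. Section 9.7 taken literally.** Control cluster-periods number 3 + 2 + 1 + 0 = 6 of 12, or 6 × 500 = 3000 planned patients. None can have received a report. The six remaining cells are all intervention cells, spread over three periods. The intervention column then equals the sum of the three period columns (rank 3 for 4 columns), so the effect in the 9.1a model cannot be estimated. With the report condition removed, all 12 cells return and the matrix has full rank (5 of 5).

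**3. Condition applied in the intervention phase only.** The protocol gives no share of patients without a report and no risk for them, so the figures here are assumptions. Let f be the share of consented intervention patients with no report and r their ADE risk. Overall risk is 15% in both phases and there is no true effect. The spurious difference, intervention minus control, is

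(0.15 − f·r)/(1 − f) − 0.15

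| f | r = 8% | r = 25% |
|---|---|---|
| 5% | 0.1460/0.95 − 0.15 = +0.4 points | 0.1375/0.95 − 0.15 = −0.5 points |
| 10% | 0.1420/0.90 − 0.15 = +0.8 points | 0.1250/0.90 − 0.15 = −1.1 points |
| 15% | 0.1380/0.85 − 0.15 = +1.2 points | 0.1125/0.85 − 0.15 = −1.8 points |

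A negative value looks like benefit. The largest entry is 1.8/4.8, a little over a third of the design difference. More extreme assumptions widen the range. With 30% lacking a report and risk half or twice that of recipients, the difference is 0.15/0.85 − 0.15 = +2.6 or 0.15/1.30 − 0.15 = −3.5 points. If f is close to zero, the bias is close to zero.

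**The case against.** The best defence is that the rest of the protocol shows what was meant. Section 9.1a fits an intervention term, Section 2.2 gives controls the same interview, and Section 9.2 counts a baseline period in the 6000. Section 9.7 says who will be analysed without saying that nobody else will be. This stands: a reader might infer that the trial planned no comparator, or that the primary comparison is impossible, and the documents taken together do not support that.

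A reader might also count intention to treat as a third, competing population. It is a principle with an exception clause, not a population. The follow-up condition in 9.1a and the discharged-alive condition in 9.7 are compatible with each other. Only the report condition conflicts. Section 9.7 does not label itself an exception, however, and an exception that removes the control phase cannot be intended.

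The one-sided selection is inferred. Section 6.1 ties weekday or weekend admission to when the report arrives and does not say that anyone goes without one. The Section 4.4 schedule places consent on days 1 to 3 and report delivery on days 1 to 4, so many very early discharges would be unconsented in either phase. The group at issue is limited to patients who consented and got no report, and its size is unknown. That limits what can be said about bias. It does not rescue the sentence: nothing says that 9.1a overrides 9.7, and 9.7's own second paragraph defines the deprescribing population without a report condition. A reader could therefore take the first paragraph's condition as deliberate.

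**Conclusion.** The contradiction is certain and needs correcting, because it concerns who enters the primary comparison. Section 9.7 requires something that Section 2.2 rules out for controls and that Section 9.1a does not ask for, and it sits badly with the intention-to-treat principle. The exclusion of some 3000 planned controls is a drafting slip, not a plan.

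The live risk is that the condition is used in the intervention phase only. Its size cannot be derived from the protocol. The range of about +1.2 to −1.8 points rests on assumed shares of 5% to 15% without a report and assumed ADE risks of 8% to 25%; it shows scale and is not an estimate. The documents do not show that any patient was dropped for this reason.

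A reader might go on to infer that patients without a 30-day interview must be treated as having missing outcomes. That does not follow from this point. Section 9.1a chooses the follow-up participants explicitly, and whether that choice is sound is a separate question.

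**What to change.** Delete from Section 9.7 the clause requiring receipt of a report in hospital, and align the section with 9.1a. Suggested content: eligible consenting patients who are discharged alive (subject to the study-unit rule in Section 5.1.b) and who took part in the post-discharge follow-up are analysed for the primary outcome by the control or intervention phase of their cluster, whether or not a report was generated, delivered or acted on. Any analysis restricted to report recipients should be labelled supplementary.

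Section 9.1b describes post-hoc analyses as already performed. The sponsor should therefore also state which population the primary analysis actually used, how many consented intervention-phase patients had no report, and, if they were left out, report this as a deviation under Section 9.6.

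The text change costs one sentence and leaves the model and sample size as they are. If the restricted set was used, the primary model has to be rerun. The protocol does not say outright that intervention-phase patients without a report were interviewed, so that should be confirmed.
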